## **Outcome assessment**

In each hospital, non-blinded coordinators (not surgeons) will ensure that the questionnaires are completed at baseline, 3 months, 12 months, 2 years, 5 years and 10 years.

## **Patient reported outcome measures (PROM)**

### **1) Primary outcome:**

The primary outcome is change in the Oswestry Disability Index (ODI) Norwegian version 2.0 [6] from baseline to 2-year follow-up. The ODI includes 10 questions about pain and activities of daily living. Each item has five response categories from no pain related disability (0) to the worst possible pain related disability (5). Responses are transformed into

an index ranging from no disability (0) to the worst possible disability (100). The ODI questionnaire is the most widely used and validated outcome measure in spinal surgery [7] [8].

## **2) Secondary outcomes:**

Secondary patient reported outcomes are changes from baseline to follow-up in the EuroQol 5-dimensional questionnaire utility index (EQ-5D), the Zurich Claudication Questionnaire (ZCQ-score), a ten point Numeric Rating Scale (NRS) for low back pain and for leg-pain, and a global perceived effect scale. Here changes at 2, 5 and 10 years will be analysed.

The EQ-5D is a generic measure of health-related quality of life. Five domains are rated: mobility, self-care, activity, pain and anxiety, each by three response categories to provide a utility index ranging from -0.59 (worst possible) to 1.0 (best possible). In addition EQ-VAS provides a single score of the patient's health condition. EQ-5D is validated for the Norwegian population. Despite its large measurement error it is often used in research for spinal conditions [9, 10]. The ZCQ is a disease specific questionnaire for lumbar spinal stenosis [11]. It includes symptom severity, physical activity and patient satisfaction during follow-up. The global perceived effect scale is a seven point scale, which is recommended for clinical trials of chronic pain conditions [12]. It has six response categories: 1 = completely recovered, 2 = much improved, 3 = slightly improved, 4 = no change, 5 = slightly worse, 6 = much worse and 7 = worse than ever. All questionnaires are validated for lumbar spinal stenosis patients [10, 11, 13] and are in close accordance with recommended PROMs for the study of low back pain conditions [14].

We will also compare the proportion of patients classified as success, between the groups. Based on change in ODI score after the operation, the patients will be dichotomized into success and non-success groups. A success is defined as a patient with an improvement in ODI score of at least 30%. This value is based on a national register study from the Norwegian Registry for Spine Surgery (NORSpine), and is also in accordance with recommendations from the IMMPACT group, when comparing clinical effect between groups [15].

The local study coordinator will record complications and adverse events, length of hospital stay, duration of surgery, blood loss and the need for blood transfusion.

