## **Statistical analyses**

All statistical analyses will be performed by a statistician blinded to the treatment given. Since this is a large randomized controlled trial, we will likely not need to adjust for potential confounding factors. However, if descriptive statistics reveal that there are imbalances in the study groups we will make comparisons with proper adjustments for such imbalances.

When comparing changes in outcomes from baseline to a fixed time point (e.g. 2, 5 or 10 years) we will use ANOVA combined with post-hoc testing for continuous outcomes. For categorical outcomes we will use standard chi-square analyses. If there is a need for confounder adjustment we will estimate the proper regression models dependent on the level of measurement of the dependent variable. Multilevel models might be used to analyse repeated measures data.

When trying to identify factors that could serve as predictors for outcome we will estimate multivariable regression models. The following factors are a priori considered to be the most relevant: treatment group, age, sex, BMI, smoking, preoperative dural sac cross-sectional area (in mm^2), percentage achieved decompression, preoperative ODI-score and preoperative NRS-score for leg pain and back pain. Bayesian information criterion (BIC) might be used as a statistical tool to select the best performing model.

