## **Timeline:**

### **Before operation:**

- Skeletal X- rays.
- MRI- scan for measuring preoperatively DSCSA.
- Following completion of the consent form the following PRO- data will be collected: ODI, ZCQ, EQ- 5D, HSCL 25, VAS for back- and leg-pain demographics, work status, smoking status and use of analgesics.

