### **3 months postoperatively ( $\pm$ 2 weeks):**

- The following PRO- data will be collected: Working status, ODI, ZCQ, EQ-5D, VAS for back- and leg-pain, patient satisfaction with treatment outcome, and patient satisfaction with treatment care.
- MRI scan to measure DSCSA postoperatively.

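### The global perceived effect scale is defined as a change from baseline that cannot be computed, and the SAP names no method for an ordinal outcome rated only at follow-up

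*Combined protocol and SAP*

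**What the plan says.** **Definition.** The SAP section on secondary outcomes opens with "Secondary patient reported outcomes are changes from baseline to follow-up in the EuroQol 5-dimensional questionnaire utility index (EQ-5D" and closes the list with "and a global perceived effect scale. Here changes at 2, 5 and 10 years will be analysed". It then describes the GPE: "It has six response categories: 1 = completely recovered, 2 = much improved, 3 = slightly improved, 4 = no change", running on to 7 = worse than ever. The same section says that the satisfaction component of the ZCQ refers to the follow-up period.

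**Schedule.** The SAP timeline lists the patient-reported data collected before operation as "ODI, ZCQ, EQ- 5D, HSCL 25, VAS for back- and leg-pain demographics, work status, smoking status and use of analgesics". The GPE is not there. From 3 months on, the list ends with "patient satisfaction with treatment outcome, and patient satisfaction with treatment care", and later visits refer back to it. The GPE is not named there either.

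**Analysis rules.** The SAP section on statistical analyses gives two unadjusted rules. For changes to a fixed time point, "we will use ANOVA combined with post-hoc testing for continuous outcomes". Then: "For categorical outcomes we will use standard chi-square analyses". Regression suited to the type of outcome is mentioned only conditionally: "If there is a need for confounder adjustment we will estimate the proper regression models dependent on the level of measurement".

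**Protocol.** The protocol's aim section also lists the patient's own rating of the effect of surgery among measurements of change. It says the groups will be compared on their average values at two years.

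**The concern.** A change score needs two measurements on the same scale. A GPE answer such as much improved already compares the present with the time before surgery, so there is nothing to ask preoperatively and nothing to subtract. The definition therefore has to be set aside in practice, and the SAP does not say what replaces it.

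The analysis section does not settle the matter. The GPE has labelled, ordered categories. It is not continuous, and a standard chi-square ignores the order. Someone working from this text could compare mean scores, test the full three-by-seven table, or split the scale into responders and non-responders. These differ in power and in what they estimate, and the choice would be left until the data exist. At stake is the interpretation of one named secondary outcome at three time points.

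**Working it through.** **1. The text, side by side.** The definition requires follow-up minus baseline. The scale is a rating of change with 4 = no change. The baseline list contains ODI, ZCQ, EQ-5D, HSCL 25 and VAS, but no GPE. The subtraction has no second term. The ZCQ as a whole is listed at baseline, but its satisfaction component concerns follow-up, so that component has no baseline either.

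**2. The plan's own sample size, as a check on inputs.** Inputs from the SAP: difference 7, SD 18, alpha 0.02 (two-sided assumed, since sidedness is not stated), power 80%, dropout 15%.

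n = 2 × (2.326 + 0.842)² × 18² / 7² = 2 × 10.036 × 324 / 49 = 132.7, so 133 evaluable per group, and 133 / 0.85 = 156.5, so 157.

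The protocol states 131 evaluable, and 131 / 0.85 = 154.1 gives the stated 155. The agreement is close enough to use 131 per group below. The documents give no power for the GPE.

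**3. Cost of ignoring the order, without assuming a category distribution.** Assume that the whole departure from equality lies in the ordered direction, so that both tests have the same noncentrality λ. Find the λ that gives the ordinal test 80% power (2 df for three arms, 1 df pairwise). Then evaluate the same λ at the Pearson degrees of freedom: (3 − 1) × (7 − 1) = 12 for three arms, (2 − 1) × (7 − 1) = 6 pairwise.

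| Comparison | Alpha | λ for 80% ordinal power | Critical value, unordered | Power, unordered | Sample-size ratio |
|---|---|---|---|---|---|
| Three arms, 12 vs 2 df | 0.05 | 9.63 | 21.03 | 49% | 1.80 |
| Three arms, 12 vs 2 df | 0.02 | 12.08 | 24.05 | 46% | 1.74 |
| Pairwise, 6 vs 1 df | 0.05 | 7.85 | 12.59 | 52% | 1.74 |
| Pairwise, 6 vs 1 df | 0.02 | 10.04 | 15.03 | 50% | 1.66 |

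The last column is the λ needed for 80% power at the larger df, divided by the λ in the third column. If only five levels are in use, the unordered power is 55–60%.

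**4. The competing readings, by simulation.** Settings: 131 per arm, two arms equal and the third shifted by a common odds ratio, 3000 replicates, three assumed seven-level distributions. The distributions and odds ratios are assumptions; the documents give none. Ranges are across distributions.

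| Test | Odds ratio 1.5 | Odds ratio 2.0 |
|---|---|---|
| Three arms, alpha 0.05: chi-square, seven levels | 20–23% | 59–66% |
| ANOVA on scores | 38–47% | 82–92% |
| Kruskal-Wallis | 44–47% | 89–92% |

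Pairwise at alpha 0.02 and odds ratio 2.0: chi-square on seven levels 42–49%, chi-square on a two-category split (levels 1–2 against 3–7) 57–66%, t-test on scores 67–79%, rank test 76–80%. With no shift, every test rejected at close to its nominal level.

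**The case against.** The strongest reply is that no sentence assigns the GPE to the chi-square rule. The SAP lists it beside scored scales, calls it a seven-point scale and speaks of changes, all of which lean towards ANOVA. The protocol's average values point the same way. On that reading the scores keep their order and most of the power. This stands. A reader might infer that the plan commits to an unordered test and so gives up a large share of its power on this outcome; the documents do not support that. The simulated sizes also rest on assumed distributions.

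A second reply is that the follow-up rating is the perceived change, so a workable reading is obvious and only the wording needs correcting. This stands in part: the observed scores can be analysed. But the definition says from baseline to follow-up, and choosing ANOVA still leaves that definition without a baseline term.

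A reader might also infer that thin cells at the worse end of the scale make a chi-square invalid. The simulation does not bear this out, since type I error stayed near nominal, and the point is not pressed.

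Finally, the SAP's own description of ZCQ satisfaction shows that its authors know it is a follow-up measure. That is fair, but the ZCQ still appears under changes from baseline without an exception.

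**Conclusion.** The point holds in two parts. First, the GPE and the ZCQ satisfaction component cannot be computed as changes from baseline. This follows from the text alone and needs no assumption. Second, the SAP does not say how the GPE is tested and has no rule for ordinal data.

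The size of the second part is conditional. If all seven levels enter a standard chi-square, 80% ordinal power becomes about 49% (three arms, alpha 0.05) or about 50% (pairwise, alpha 0.02), given a purely ordered shift. If mean scores are compared, most of the power remains.

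A reader might take this to weaken the trial's main result. It does not: it concerns secondary outcomes, and the primary ODI analysis and 155 per group are untouched. It should be corrected, but it is not critical.

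**What to change.** - Remove the GPE and ZCQ satisfaction from the outcomes defined as change from baseline, and define both as observed values at follow-up.
- Name one ordinal method for the GPE at 2, 5 and 10 years: a proportional-odds model reporting common odds ratios, or Kruskal-Wallis with pairwise rank tests at the plan's 2% level. The plan states that level for its pairwise comparisons but not expressly for secondary outcomes, so say that it applies.
- Analyse ZCQ satisfaction as an observed follow-up score.
- Keep chi-square for binary outcomes such as ODI success.
- In the same edit, reconcile the stated six response categories with the seven listed, and name the GPE in the follow-up schedule or say which listed item it corresponds to.

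The cost is a few sentences in the SAP and no new data beyond what the outcome section already intends. A proportional-odds model needs a routine check of its assumption; Kruskal-Wallis does not.

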### **12 months postoperatively ( $\pm$ 1 month):**

- -The same PRO-data as at 3 months will be collected.

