The surgical treatment of LSS is to perform a decompression. To achieve relief of the stenosis, one must remove the flaval ligaments, and the lamina (whole, or parts of it) at the disc level, and carry out a partial medial facetectomy to decompress the nerve-root in the lateral recess. The traditional operation is a laminectomy, which involves the total removal of the lamina and the flaval ligaments, with a medial facetectomy. This procedure also removes much of the posterior ligamenture of the spine, and is considered to be a relatively invasive procedure; it is also prone to postoperative instability of the operated spinal segment. In recent decades bilateral laminotomy has become an alternative to a laminectomy [2,19]. This is a less invasive procedure, in which parts of the lamina are retained, and the interspinal and supraspinal ligaments are mostly kept intact. This procedure is therefore considered to be better at preserving stability. More recently a unilateral decompression has been described [21], referred to as a “bilateral laminotomy with crossover technique”. The access to the spinal canal is unilateral, and the ipsilateral side is decompressed as usual, whereas the contralateral side is decompressed using a crossover technique. This has theoretical advantages by preserving more of the paraspinal muscles, ligaments and bony structures. A third alternative is to do a spinous process osteotomy [13]. This procedure also involves unilateral release of the paraspinal muscles, and an osteotomy of the spinous process at the

base, above the actual level. These osteotomies facilitate access to the spinal canal with improved visibility, which may be an advantage over the other methods.

Several studies have been conducted to compare laminectomy and bilateral laminotomies [3,8,11,24,26,34,35]. A Cochrane review article from 2005 state that one cannot conclude which procedure gives superior clinical results in these studies [12]. In our opinion later studies have not fulfilled this purpose either. Some studies compare “bilateral laminotomy” with “unilateral laminotomy with crossover”. One of these studies shows inferior results with “unilateral laminotomy with crossover” [35], and two studies show equal clinical results between the two procedures [6,17]. There are no studies comparing spinous process osteotomy with other procedures.

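### Patient-reported outcomes at 3 and 12 months have no prespecified comparison between techniques; one baseline-adjusted repeated-measures model would supply it from data already planned

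*Combined protocol and SAP*

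**What the plan says.** **Collection.** SAP section 3, Outcome assessment, has local coordinators ensure that "the questionnaires are completed at baseline, 3 months, 12 months, 2 years, 5 years and 10 years". The SAP Timeline lists for 3 months "Working status, ODI, ZCQ, EQ-5D, VAS for back- and leg-pain, patient satisfaction with treatment outcome", and for 12 months "The same PRO-data as at 3 months will be collected". The protocol's Timeline gives the same set at both visits.

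**Committed comparisons.** The primary outcome is the change in ODI "from baseline to 2-year follow-up", and the protocol's Aim of the study also sets it at two years. For the secondary patient-reported outcomes the SAP says "Here changes at 2, 5 and 10 years will be analysed"; the protocol places them at two years. The protocol sets the responder comparison at 24 months. The SAP's version of that comparison names no visit.

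**Method.** SAP section 4, Statistical analyses, plans ANOVA with post-hoc tests on change to a fixed time point, giving 2, 5 and 10 years as examples. It adds: "Multilevel models might be used to analyse repeated measures data".

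**Missing scores.** The protocol's Statistics section carries the last value forward for dropouts. In a sensitivity analysis, crossovers receive their last score before crossing over. The SAP's Sample size section promises imputation if missing data exceed 15%, without naming a method.

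**The concern.** The SAP's main objective asks whether one technique is superior to the others. The trial is open label and its main outcomes are self-reported. In that setting the plan should settle in advance which visits are compared and how. Here the early visits are collected in full but assigned no comparison, and the one method that could use them is optional.

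Two things are at stake. First, if the techniques differ at 3 or 12 months and are alike by 2 years, the committed analyses will not show it. An early comparison added later would carry the weakness of a visit and outcome chosen after the data were seen. Second, the 2-year comparison makes poor use of early scores from patients who are later lost. They are either carried forward unchanged, which assumes no change up to 2 years, or handled by an unspecified imputation.

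**Working it through.** **1. Collection set against commitment**

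| Visit | Outcomes collected | Comparison between techniques committed |
|---|---|---|
| 3 months | yes | none |
| 12 months | yes | none |
| 2 years | yes | ODI (primary); secondary outcomes |
| 5 years | yes | secondary outcomes (SAP) |
| 10 years | yes | secondary outcomes (SAP) |

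Two of five follow-up waves have no committed comparison. With 465 patients that is at most 465 x 2 = 930 questionnaire sets, if nobody is lost before 12 months.

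**2. How early scores can still reach the 2-year result**

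At the planned 15% loss, 465 x 0.15 = 69.75, so about 70 patients lack a 2-year score. Last value carried forward uses one ODI score from each, which is the baseline score if the patient left before 3 months. So at most about 70 early ODI scores enter the main 2-year comparison by this route. The crossover sensitivity analysis may add a few. The SAP's imputation applies only above 15%, and whether it would use early scores is not stated.

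**3. Could early contrasts be informative?**

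Inputs from the SAP's Sample size section: difference 7, SD 18, two-sided level 0.02, power 80%, 155 per group.

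The plan's own figure first: n = 2 x SD² x (z₀.₉₉ + z₀.₈₀)² / difference² = 2 x 324 x (2.326 + 0.842)² / 49 ≈ 133 evaluable per group, and 133/0.85 gives 157. The protocol uses 131 evaluable, and 131/0.85 = 154.1, which rounds up to 155. The plan's figure is reproduced to within 3%.

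Power at a given visit = Φ(7 / (18 x √(2/m)) − 2.326), with m evaluable per group. The detectable difference at 80% power = 18 x √(2/m) x (2.326 + 0.842).

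| Loss at the visit | m = 155 x (1 − loss) | Power | Detectable difference |
|---|---|---|---|
| 5% (assumed) | 147.25 | 84.4% | 6.6 |
| 10% (assumed) | 139.5 | 82.2% | 6.8 |
| 15% (the plan's rate) | 131.75 | 79.7% | 7.0 |

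The t distribution gives values about half a percentage point lower (84.0%, 81.7%, 79.2%). The documents give neither the loss nor the SD at the early visits, so the first two rows assume both. They show only that early ODI contrasts would be about as informative as the 2-year contrast. The gap in the plan does not depend on them.

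**4. What a baseline-adjusted model gains**

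Let ρ be the correlation between baseline and follow-up, with equal variance σ² at both. A change score has variance 2(1 − ρ)σ². With the baseline score as covariate the residual variance is (1 − ρ²)σ². The ratio of the second to the first is (1 + ρ)/2, which is below 1 for any ρ below 1. The documents give no ρ, so the size of the gain is left open. Fitting all visits together also lets patients with only early follow-up contribute without carrying a score forward, under a missing-at-random assumption.

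**The case against.** The strongest reply is that late time points fit the stated aims. The SAP's main objective refers to sustaining long-term results, and the protocol's Clinical results section makes long-term outcome the main goal. Speed of recovery is not an objective, and restricting visits to limit secondary testing is a legitimate choice. This stands. It is a reason to keep early contrasts secondary, but not to leave their status unstated.

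A reader might infer that the early data go unused, or that the trial cannot speak to early recovery. The documents do not support this. The fixed years in Statistical analyses are only examples, the optional multilevel model could include every visit, and last value carried forward brings some early ODI scores into the 2-year comparison. The data will exist and can be explored; what is missing is a prespecified basis.

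A reader might also infer from the protocol's background that a less invasive technique should show its benefit first at the early visits. The sentence "This has theoretical advantages by preserving more of the paraspinal muscles, ligaments and bony structures" concerns the unilateral technique and says nothing about timing. The same section links retained structures to stability and credits the osteotomy with better visibility. The SAP describes all three techniques as retaining the midline. Early benefit is a clinical premise, not a statement in the plan.

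Two further points stand in part. The protocol does compare operation time, bleeding, complications and hospital stay, so the perioperative period is covered, but these are not patient-reported. The SAP's statistician is blinded to treatment, which limits selective analysis but does not fix which visits are reported.

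**Conclusion.** The point holds as a gap in prespecification combined with an inefficient analysis. Two of five follow-up waves have no committed comparison between techniques. Neither the list of example years nor the optional model fills that gap, because neither names an early visit, an outcome or a contrast. Within the committed main analysis, early scores matter only for the patients lost before 2 years, about 70 at the planned rate.

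This does not invalidate the primary objective or the 2-year ODI comparison. It should be put right before the data are analysed, because the better method uses data already planned. The conclusion rests on the text alone. The early power figures rest on an assumed loss of 5% to 10% and on an SD of 18 at those visits.

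**What to change.** In SAP section 4, replace the optional multilevel wording with one mixed model for each continuous outcome: ODI, NRS back pain, NRS leg pain, ZCQ and EQ-5D. Each model has technique, visit (3, 12 and 24 months) and their interaction, with the baseline score as covariate and correlation between a patient's visits allowed for. Keep the three pairwise 2-year ODI contrasts as primary.

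In SAP section 3, Secondary outcomes, add 3 and 12 months to the listed years. Report those technique contrasts with confidence intervals, labelled secondary and not confirmatory. Use one name for the pain scale, since the Timeline calls it VAS and the outcome section NRS.

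The cost is SAP wording and analysis time, with no new patients, visits or data. The downside is about 5 outcomes x 2 visits x 3 pairs = 30 more secondary contrasts, which must not support confirmatory claims.
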